# Introduction

### Background and Rationale

Acute respiratory failure is a common reason for admission to the Intensive Care Unit (ICU), and it is estimated that 13-20 million patients are mechanically ventilated worldwide annually^1^ with more than a third dying during the hospital admission, although studies suggest that the mortality have improved in recent years.^2–45^

Endothelial dysfunction has been proposed as a plausible link between critical illness and multiorgan failure^6^ and two Danish Randomized Controlled Trials (RCT) are currently testing the prostacyclin analogue Ilomedin as a targeted treatment against endotheliopathy in trauma and septic shock.

In experimental models, pathologic stimuli to the pulmonary endothelium results in the inflammation and noncardiogenic pulmonary oedema that are hallmarks of ARDS.^7–9^

In ARDS increased permeability of the intercellular connections between endothelial cells leads to fluid accumulating in the alveoli. A yet unpublished study found that Platelet Endothelial Cell Adhesion Molecule (PECAM-1) is the best marker for this interruption of the cell-cell junctions between the endothelial cells.

In clinical studies, soluble thrombomodulin (sTM) and Syndecan-1 are valid markers of damage to the profound endothelium and endothelial glycocalyx, respectively.^10^ In critically ill patients, both markers increase with more severe disease and predicts liver and renal failure.^10,11^ Increased sTM levels are associated to fewer ventilator free days,^12^ organ failure^13,14^ and mortality^14^ in patients with ARDS.

Syndecan-1 associates with acute respiratory failure in patients with pulmonary sepsis^15^ and severe sepsis after resuscitation with large volumes of fluids.^16^ Nevertheless, surprisingly both markers correlates poorly with hypoxaemia at ICU admission and need for mechanical ventilation.^10^

### Objectives

The broader aim of the study is to expand the knowledge on the connection between endothelial dysfunction and patient-important outcomes in the setting of critically ill patients with acute respiratory failure. If a connection between the duration of mechanical ventilation and endothelial dysfunction is found it could lead to better prognostication and identification of the sickest patients at ICU-admission. This could pave the way for clinical trials testing a targeted treatment against the endotheliopathy to shorten the time that mechanical ventilation is required.

The objective of the study is to estimate the impact of endothelial dysfunction as measured with sTM, Syndecan-1 and PECAM-1 on the time to liberation from mechanical ventilation in a general ICU population admitted with acute respiratory failure.

# Methods

### Study design

The Metabolomics study investigates the role of the endothelium in patient-important outcomes in a cohort of critically ill adults admitted to the ICU.

We present here an analysis of a subpopulation of the Metabolomics study.

The study is reported in accordance with the STROBE-recommendations^17^

### Sample size

As previous data on the levels of sTM, Syndecan-1 and PECAM-1 in a critically ill population of patients with acute respiratory failure are very scarce, formal power calculations were not possible to perform and the results should be considered exploratory.

### Outcome Assessment

Patients were followed for 30 days after inclusion for collection of clinical data from their ICU-stay including timing of liberation from mechanical ventilation and were subsequently followed for a year for the occurrence of death from any cause.

# Statistical Principles

A p-value below 0.05 is considered significant. 95% Confidence Intervals (95% CI) are presented along with point estimates where feasible.

Results from both the univariable and multivariable analysis are presented where relevant.

No correction for multiple comparisons is performed, as all study results will be regarded as exploratory.

# Trial Population

### Screening data

The ICU at Copenhagen University Hospital – North Zealand, Copenhagen, Denmark is a 12 bed, mixed surgical/medical ICU with around 900 admissions per year.

Between November 2016 and June 2019 all patients presenting to the ICU were screened for inclusion in the Metabolomics Study.

Unfortunately, no screening log was kept at the time.

### Eligibility

The inclusion criteria consisted of age > 18, acutely admitted to the ICU and a presumed stay > 24 h. The exclusion criteria were non-obtainable informed consent or active treatment deemed futile by the treating clinician.

Included patients had study blood samples drawn daily for the first 5 days of their ICU-stay or until death or discharge, whichever came first.

For the present study in the Metabolomics cohort, only patients that presented with acute respiratory failure are included. Acute respiratory failure is defined as patients receiving either Invasive (IV) or Non-Invasive Ventilation (NIV) on the first day of ICU-admission.

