# Analysis

### Outcome Definitions

The primary outcome is time in days to liberation from mechanical ventilation. Liberation from mechanical ventilation is defined to occur on the second of two consecutive ICU-days without the need for either IV or NIV. Liberation from mechanical ventilation was also considered to occur on the day of ICU discharge if cessation of mechanical ventilation occurs on the same day as ICU-discharge in patients that are not readmitted to the ICU within two days. The competing risk of death is said to occur if patients died before or within 24 hours from liberation from mechanical ventilation. Patients are censored if they were moved to a different hospital while still receiving mechanical ventilation or at 30 days if still receiving mechanical ventilation.

Secondary outcomes are the risk of death from any cause at 30 days, PaO2/FiO2-ratio (PAF-ratio) on the first day of ICU-admission and last measured PAF-ratio in patients dying within 5 days from inclusion.

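### The primary outcome has no event or censoring date for patients who leave the ICU still on NIV, and neither the entry rule nor the liberation rule separates new NIV from a home regimen

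*SAP*

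**What the plan says.** **Entry.** Eligibility in the SAP states: "Acute respiratory failure is defined as patients receiving either Invasive (IV) or Non-Invasive Ventilation (NIV) on the first day of ICU-admission". The parent study requires an acute ICU admission with an expected stay of more than 24 hours. The exclusions do not mention ventilation before admission: "The exclusion criteria were non-obtainable informed consent or active treatment deemed futile by the treating clinician".

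**Event.** Outcome Definitions gives two routes to liberation. The main one is: "Liberation from mechanical ventilation is defined to occur on the second of two consecutive ICU-days without the need for either IV or NIV". The other dates liberation at ICU exit, under this condition: "if cessation of mechanical ventilation occurs on the same day as ICU-discharge in patients that are not readmitted to the ICU within two days".

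**Competing event.** "The competing risk of death is said to occur if patients died before or within 24 hours from liberation from mechanical ventilation".

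**Censoring.** "Patients are censored if they were moved to a different hospital while still receiving mechanical ventilation or at 30 days if still receiving mechanical ventilation".

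**Data source.** Outcome Assessment says: "Patients were followed for 30 days after inclusion for collection of clinical data from their ICU-stay including timing of liberation from mechanical ventilation". It does not say whether NIV after ICU discharge is recorded.

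**Covariates.** Under Variables, the adjustment set includes a history of COPD but not home ventilation. Baseline respiratory treatment is collected (Baseline Patient Characteristics) but has no stated role in the models.

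**The concern.** The objective is the relation between endothelial markers and time to liberation in patients with acute respiratory failure. Two gaps affect that outcome.

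- **New and habitual NIV are not separated.** A patient on long-term nocturnal NIV who is admitted acutely for another reason can enter through the habitual device. If continued use counts as need, that patient cannot have the event.
- **One way of leaving the ICU has no rule.** A patient who goes to a ward of the same hospital, or home, while still on NIV meets neither liberation route and neither early censoring rule. This covers patients stepped down on acute NIV as well as home users, so the gap does not depend on home users being in the cohort.

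Patients kept at risk without being able to have the event accumulate in the late risk sets, where few others remain. If their share differs between marker levels, the primary hazard ratio is biased. Two analysts following the same text could also date these patients differently and report different estimates. Adjustment for COPD is not a remedy, because a history of COPD does not identify home NIV.

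**Working it through.** The SAP gives no sample size, event count or number of affected patients, so there is no figure of its own to reproduce. The check is a trace through the rules, followed by an illustration with assumed inputs.

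**1. Trace: a patient on NIV every ICU day who goes to the ward or home on NIV**

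| Rule | Result |
|---|---|
| Entry: IV or NIV on day 1 | Met |
| Exclusions | Do not apply |
| Two consecutive ICU days free of IV and NIV | Not met, if use is taken as need |
| Ventilation stops on the ICU discharge day | Not met |
| Moved to a different hospital while ventilated | Does not apply |
| Death before liberation | Only if it occurs |
| Still ventilated at day 30 | The only remaining rule |

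The last rule needs ventilation status on day 30, while Outcome Assessment describes data from the ICU stay.

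**2. Weight in the late risk sets (all inputs assumed)**

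Let l be the daily liberation hazard, d the daily death hazard, and f the share who cannot be liberated. Their share of the risk set at day t is

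f·exp(−d·t) / [(1−f)·exp(−(l+d)·t) + f·exp(−d·t)].

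With l = 0.15, d = 0.03 and t = 15:

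- f = 2%: 0.02 × 0.638 = 0.0128, against 0.98 × 0.0672 = 0.0659. The share is 0.0128 / 0.0787 = 16%.
- f = 5%: 0.05 × 0.638 = 0.0319, against 0.95 × 0.0672 = 0.0638. The share is 0.0319 / 0.0957 = 33%.

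**3. Effect on the liberation HR (simulation, all inputs assumed)**

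Two marker groups of 20,000 each. The low-marker liberation hazard is 0.15/day and the true HR (high against low) is 0.60, so the high-marker hazard is 0.15 × 0.60 = 0.09/day. Death hazards are 0.02/day (low) and 0.045/day (high), over 30 days. A share of each group leaves the ICU on NIV. These patients are either kept at risk to day 30 or censored at an assumed ICU exit on day 3. A Cox model for liberation is then fitted. The results are means of 20 runs. Where two values appear, the first ignores deaths among the carried patients and the second lets deaths end their time at risk.

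| Share, low / high marker | HR, carried to day 30 | HR, censored at day 3 |
|---|---|---|
| 0% / 0% | 0.60 | 0.60 |
| 1% / 1% | 0.61 | 0.60 |
| 2% / 2% | 0.62 | 0.60 |
| 4% / 4% | 0.63–0.64 | 0.60 |
| 3% / 1% | 0.67–0.66 | 0.60 |
| 6% / 2% | 0.72–0.71 | 0.61 |
| 2% / 6% | 0.55–0.57 | 0.59 |

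Equal shares pull the HR slightly towards 1. Unequal shares move it either way, by up to about 0.12 in these examples. Censoring at ICU exit leaves it within about 0.01 of the true value.

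**The case against.** **The 30-day carry-forward.** A reader might infer that the SAP carries these patients as ventilated for 30 days. It does not say so. Day-30 censoring is conditional on still being ventilated, and with data tied to the ICU stay an analyst might instead censor at ICU discharge or count discharge as liberation. Transfers to another hospital and deaths also end follow-up earlier. This stands, and it limits the point to an undefined outcome whose literal reading runs to day 30.

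**Home users can never be liberated.** This too might be inferred. The liberation rule speaks of *need*, not receipt, which leaves room to disregard habitual use. The SAP does not say that it should be disregarded, so the ambiguity remains.

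**A real marker effect is masked.** The SAP gives neither the share of such patients nor its relation to marker level. Masking requires more of them among low-marker patients; the reverse exaggerates the effect. With equal shares of 1 to 4% the distortion is small. No direction can be claimed.

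**The study is exploratory.** Sample size and Statistical Principles both say so, and this lowers the stakes. The primary outcome still needs a date for every patient. Results are judged at p < 0.05 and are meant to inform prognostication and later trials.

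**The data may already identify home users.** Baseline respiratory treatment is collected and might serve. The SAP assigns it no such use.

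**Conclusion.** The point holds as a gap in the definition of the primary outcome. Entry and liberation do not separate new NIV from a home regimen, and no event or censoring date is given for leaving the ICU on NIV within the same hospital or to home. On the literal reading such patients stay at risk to day 30 on data that may not exist.

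The size is unknown, because the number affected is not stated. Under the assumed constant hazards and a true HR of 0.60, the effect is negligible to slight with small equal shares. It is material only if shares differ by marker level: about 0.71 with 6% low against 2% high, and about 0.55 with the reverse. The choice of date matters too. For 6% against 2%, the HR is about 0.71 if patients are carried to day 30 and about 0.61 if they are censored at an ICU exit on day 3. These figures show sensitivity and are not estimates for this cohort. The change should be made because it is cheap and removes a choice that would otherwise be made with the data in hand.

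**What to change.** 1. **Outcome Definitions.** For patients leaving the ICU on NIV for a ward of the same hospital or for home, take the last NIV day from the EMR, up to day 30, and date liberation from it. If it cannot be retrieved, censor at ICU discharge and not at day 30.
2. **Variables.** Add ventilation at home before admission to the EMR adjudication already planned for COPD, heart failure and respiratory infection, which is blinded to the markers and the primary outcome.
3. **Eligibility and Outcome Definitions.** For this analysis, exclude patients whose only day-1 ventilation is their home regimen. For other home users, count return to the habitual regimen as liberation.
4. **Analysis Methods.** Report the number of patients in each category, and add a sensitivity analysis that keeps them all and applies the present rules literally.

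Cost: one more EMR item, a few sentences, and a few patients excluded or recoded. The exclusion narrows the cohort slightly, and the sensitivity analysis shows whether that matters.

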### Baseline Patient Characteristics

The characteristics collected at baseline include:

- Patient demographics (age and gender)
- Chronic comorbidities (a history of heart failure, hypertension, diabetes, stroke, prior MI etc.)
- Primary reason for ICU-admission (as per SAPS 3 categories)
- Category of ICU-admission (medical, surgical, acute, elective)
- Timeline parameters (time of inclusion, time of ICU-admission, time of hospital admission etc.)
- Infection status at admission
- ICU-admission source (operating theatre, ward, emergency department etc.)
- Physiology at baseline (PAF-ratio, blood pressure, pulse etc.)
- Therapy at baseline (noradrenaline, insulin etc.)
- Respiratory therapy at baseline

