### Variables

The explanatory variables of interest are sTM, Syndecan-1 and PECAM-1. These are continuous and presented in ng/ml. They will also be introduced to the regression models as categorical variables divided into three groups: =< 25^th^ percentile, > 25^th^ and =< 75^th^ percentile, > 75^th^ percentile

To be controlled for in the multivariable analyses are the following known predictors of poor outcomes in the ICU: Gender, Age, A history of Chronic Inflammatory Pulmonary Disease (COPD), Septic Shock at ICU-admission, A history of Heart Failure, Worst PAF-ratio on the first day of ICU-admission, The presence of Respiratory Infection at ICU-admission, Acute Kidney Injury during the first day of ICU-admission and highest Bilirubin during first day of ICU-admission.

Septic shock is defined in accordance with the “Third international consensus definition for sepsis” as suspected or confirmed infection plus the need of vasoactive medication to maintain a mean arterial blood pressure of 65 and a blood lactate of 2 or more.^18^

COPD, Heart Failure and Acute Respiratory Infection are adjudicated by one author ([name]) based on information from the EMR without knowledge of the results of the primary outcome or of the values of sTM, Syndecan-1 or PECAM-1.

PAF-ratio is calculated with information from the EMR as the values of PaO2 and FiO2 giving the lowest ratio on a given day of ICU-admission.

Acute Kidney Injury is defined as stage 2 or more from the KDIGO guidelines and calculated based on the worst creatinine during the first day of ICU-admission.^19^ Baseline creatinine is defined as the median of all creatinine levels from 180 to 8 days prior to ICU-admission. In patients without a baseline creatinine, the creatinine levels is estimated with revised Lund-Malmö formula assuming a normal GFR of 70 ml/min/1,73m2.^20^

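### Medical/surgical admission category and day-1 ventilation mode are collected but enter neither the liberation nor the mortality model, so residual confounding by case mix is possible

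*SAP*

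**What the plan says.** Eligibility (SAP) sets the entry rule for this analysis: "Acute respiratory failure is defined as patients receiving either Invasive (IV) or Non-Invasive Ventilation (NIV) on the first day of ICU-admission". It gives no hypoxaemia threshold and no restriction on why the patient was ventilated. The parent cohort is equally broad: "The inclusion criteria consisted of age > 18, acutely admitted to the ICU and a presumed stay > 24 h". Screening data describes the unit as a "mixed surgical/medical ICU with around 900 admissions per year", and Objectives states the target as the effect of the markers "in a general ICU population admitted with acute respiratory failure".

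Baseline Patient Characteristics lists among the data collected "Respiratory therapy at baseline", "Category of ICU-admission (medical, surgical, acute, elective") and "Primary reason for ICU-admission (as per SAPS 3 categories").

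Variables introduces the adjustment set with "To be controlled for in the multivariable analyses are the following known predictors of poor outcomes in the ICU". The nine items are gender, age, COPD, septic shock, heart failure, worst day-1 PAF-ratio, respiratory infection, acute kidney injury and highest day-1 bilirubin. Analysis Methods uses this set in one Cox model per marker for liberation, and again for 30-day mortality. It plans no stratification, subgroup or sensitivity analysis by ventilation mode or admission category.

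**The concern.** A patient ventilated after emergency surgery and a patient on mask ventilation for COPD can both enter, and both are analysed with one baseline hazard. The outcome is the duration of ventilation, so the kind of ventilation at time zero and the kind of admission are plausible determinants of it. If either is also related to sTM, Syndecan-1 or PECAM-1 after the nine covariates, the marker hazard ratio absorbs part of that relation. The stated objective is to estimate the impact of endothelial dysfunction, so what is at stake is whether the reported hazard ratio reflects the marker or the case mix. The data are in hand, and the SAP gives no reason for leaving the two variables out.

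**Working it through.** The SAP states no sample size, event count or expected effect, so there is no figure to reproduce. The check has two parts.

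**1. What is collected against what is modelled**

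| Variable | Collected (Baseline Patient Characteristics) | In the nine covariates (Variables) | Other use (Analysis Methods) |
|---|---|---|---|
| Medical/surgical category | yes | no | none |
| Day-1 mode (IV or NIV) | yes; also needed to apply eligibility | no | none; not among the interactions named |
| Reason for admission | yes, SAPS 3 categories | only through proxies such as respiratory infection and septic shock | none |

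All patients are acute admissions, so the acute/elective part of the category should hardly vary. Medical versus surgical is the informative part.

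**2. Possible size, on assumed inputs**

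None of the inputs below comes from the SAP.

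*Admission category.* Approximate shift in the marker's log hazard ratio per SD when category is omitted:

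shift = ln(HR of category) × p(1 − p) × d

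Here p is the surgical share and d is the marker difference in SD (surgical minus medical) that remains after the listed covariates. With p = 0.25, p(1 − p) = 0.1875. The true marker hazard ratio is taken as 0.80 per SD.

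| HR, surgical vs medical | d | shift | estimated HR |
|---|---|---|---|
| 1.3 | 0.2 | 0.262 × 0.1875 × 0.2 = 0.010 | 0.80 × exp(0.010) = 0.81 |
| 1.3 | 0.5 | 0.262 × 0.1875 × 0.5 = 0.025 | 0.82 |
| 2 | 0.2 | 0.693 × 0.1875 × 0.2 = 0.026 | 0.82 |
| 2 | 0.5 | 0.693 × 0.1875 × 0.5 = 0.065 | 0.85 |
| 2 | 1.0 | 0.693 × 0.1875 × 1.0 = 0.130 | 0.91 |

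If surgical patients have lower markers, the sign of d flips and the range becomes 0.80 × exp(−0.010) = 0.79 down to 0.80 × exp(−0.130) = 0.70. At d = 0 the shift is zero.

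A simulated Cox model (20,000 patients, HR 2, competing death, 30-day censoring) agrees closely. Without category it gave 0.86 at d = 0.5, 0.89 at d = 1 and 0.77 at d = −0.5. With category it gave 0.80 to 0.81.

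*Ventilation mode.* Take no true marker effect, a liberation hazard ratio for NIV versus IV of 1.5 to 3, and an NIV share in high- versus low-marker patients from 30% vs 40% to 10% vs 50%. The spurious marker hazard ratio is approximately

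[p_high(HR − 1) + 1] / [p_low(HR − 1) + 1]

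- Mild end: (0.3 × 0.5 + 1)/(0.4 × 0.5 + 1) = 1.15/1.20 = 0.96.
- Strong end: (0.1 × 2 + 1)/(0.5 × 2 + 1) = 1.2/2.0 = 0.60.
- Equal NIV shares: exactly 1.00.

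Simulation over the same settings (50,000 patients, 30-day censoring, competing death) gave 0.97 to 0.72 without mode and 0.98 to 1.02 with it. Neither the formula nor the simulation includes the nine covariates, so these figures show the mechanism and do not forecast the bias. They also treat mode purely as a confounder. If mode is partly a consequence of the marker, some of this difference is genuine effect.

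**The case against.** The strongest reply is that nothing here is an error. The target is a general ICU population, the endpoint treats IV and NIV alike, consistently with eligibility, and choosing nine predictors over two others is a preference. Several of the nine already describe why the patient is ventilated. Every result is labelled exploratory. Model assumptions will be checked, and the interactions are introduced only as examples, so a marker-by-mode term is not ruled out.

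Much of this stands. There is no internal contradiction, and the listed covariates do part of the work. It does not dispose of the point. A broad target population does not remove the need to control confounding within it. The listed covariates do not identify postoperative patients or separate mask from tube. The exploratory label limits what may be claimed but leaves the estimate as it is. Checks of fit do not reveal an omitted confounder.

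Three stronger readings are tempting and should be resisted:

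- **That admission category is a confounder.** The SAP has no data linking category to the markers or to liberation once the nine covariates are in the model, and the direction is unknown.
- **That pooling the modes makes the primary model non-proportional.** This is conjecture, and the promised assumption checks partly cover it.
- **That the primary model should be stratified by mode.** Endothelial injury may itself influence whether a patient is intubated. Stratifying would then remove part of the effect the study sets out to estimate. Day-1 PAF-ratio and kidney injury, already in the model, raise the same issue.

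**Conclusion.** The point holds as a possible, unquantified residual confounding that the SAP could guard against with data it already has. On the assumed range, a hazard ratio of 0.80 per SD would be reported as about 0.81 to 0.91 if surgical patients are liberated faster and have higher markers, and as about 0.79 to 0.70 if their markers are lower. The true bias may be zero. These figures rest on an assumed 25% surgical share, hazard ratio of 1.3 to 2 and residual marker difference of 0.2 to 1 SD.

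The case is firmer for admission category than for mode. Category is settled at ICU admission, before the study samples are drawn, so adjusting for it carries little risk. Mode may lie on the causal path, so it belongs in a sensitivity analysis. This is a moderate weakness in the choice of covariates and should be corrected.

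**What to change.** - **Variables and Analysis Methods:** add medical versus surgical admission category to the covariates of the liberation and 30-day mortality models.
- **Primary liberation models:** keep them unstratified by ventilation mode.
- **Sensitivity analysis:** prespecify one per marker for liberation, with the baseline hazard stratified by day-1 mode (IV versus NIV). State that mode may partly mediate the marker's effect, so a difference from the primary result is not by itself evidence of confounding.

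No new data are needed. The cost is one more coefficient per model and a few extra fits: three if each marker is entered in one form, six if both the continuous and the three-group forms are repeated. Since no patient or event count is given, the SAP should confirm that the number of events supports the added term alongside any splines and interactions.
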